#### Secondary outcomes

To assess negative mental health consequences of stress, reflected as depressive symptoms, we will use the 15-item version of the German adaptation of the Center for Epidemiological Studies Depression Scale (CES-D) [52, 53]. In addition, we will use the German version of the Brief Resilience Scale (BRS) [54, 55] to assess changes in participants’ ability to recover from stress. To assess work-related stress we will use the relatively new Perceived Occupational Stress scale (POS) [56], translated to German.

We will use different measures for the training evaluation. To assess user satisfaction with the intervention received, we will use the Client Satisfaction Questionnaire (CSQ) [57, 58] and the adaptation CSQ-I [59] to measure satisfaction with Internet-based interventions. Adherence to the interventions will be measured using log data from iSMT participants and self-rated questions for all participants (e.g., “How often have you tried to apply tips and techniques you have learned in your daily life?”). Within gSMT, trainers will be instructed to record participants’ attendance at every training session. We also will assess the extent to which trainers adhere to the training manual (e.g., “How well did you manage to communicate the intended training content?”).

#### Cost-effectiveness measures

To collect health service utilization and productivity losses, we will use the Treatment Inventory of Costs in Psychiatric Patients (TIC-P) [60], adapted to the German context. This questionnaire includes different single questions to estimate the impact of presenteeism on productivity losses. To estimate productivity loss due to impaired performance directly, we adapted an item extracted from the Health and Labor Questionnaire (HLQ) [61]: “If you now have to catch up on work that you have not done in the last 4 weeks due to your health problems, how many hours would you have to work?”. For cost-utility analyses, we will calculate quality-adjusted life years (QUALYs), based on the Assessment of Quality of Life (AQoL-6D) [62].

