## Methods

### Study design

The declaration of Helsinki for Ethical Principles for Medical Research Involving Human states that “The benefits, risks, burdens and effectiveness of a new intervention must be tested against those of the best proven intervention(s)” [38]. Accordingly, we will test the non-inferiority and cost-effectiveness of the relatively new iSMT intervention “GET.ON Stress” [29] against the best proven and probably most adopted intervention for stress management in Germany speaking countries, that is the gSMT intervention “Gelassen und sicher im Stress – calm and safe under stress” [32, 33]. In a randomized controlled trial, one group of participants will receive access to iSMT, whereas another group will participate in gSMT.”

Outcome assessments will take place at baseline (T1), and both three months (T3) and six months (T4) after allocation to the study conditions. To mimic real-life occupational practice, participants in iSMT will be granted access to the intervention immediately after randomization, whereas participants in gSMT will have to wait until a sufficiently large number of participants has been recruited and randomized into this condition to fill group sessions. For this reason, participants in each condition will also need to attend in a short extra assessment (T2) right before their first training session.

The primary outcome will be the level of perceived stress at T3. There will be no restrictions to the use of other care as usual (CAU). This study protocol describes the design of the pragmatic trial based on Standard Protocol Items: Recommendations for Interventional Trials (SPIRIT) guidelines [39]. The study also will be conducted in accordance with the Consolidated Standards of Reporting Non-inferiority Trials (CONSORT) [27].

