### Outcome measures

#### Primary outcome

The primary outcome will be the level of self-rated stress (Table 3), measured using the Perceived Stress Scale (PSS-10) [49], a validated measure of stress that has been used extensively during evaluations of both in-person and Internet-based stress-management interventions. The PSS-10 assesses the extent to which participants experience their lives as stressful (e.g., as overstraining, unmanageable, and/or unforeseeable over the past month). It consists of ten items, each having the following 5-point Likert scale response options of 0 = never; 1 = almost never; 2 = sometimes; 3 = fairly often; and 4 = very often (summation score range 0–40). In this trial, respondents will answer items referring only to the past week. The German version of the scale has been validated in the general population [50]. An online version of the German scale has also been validated in samples of German employees, exhibiting good reliability with McDonald’s omega (ω) = .89 and good measurement invariance [51].

**Table 3 Tab3:** Outcome measures and assessment points

Outcome measures	T0	T1	T2	T3	T4
Perceived Stress Scale (PSS)	✓	✓	✓	✓	✓
Center for Epidemiological Studies on Depression Scale (CES-D)	-	✓	-	✓	-
Brief Resilience Scale (BRS)	-	✓	-	✓	-
Perceived Occupational Stress (POS)	-	✓	-	✓	-
Technology Readiness (TRI 2.0)	-	✓	-	-	-
Patient Questionnaire on Therapy Expectation and Evaluation (PATHEV) – adapted for stress management training	-	✓	-	-	-
Effort-Reward-Imbalance Questionnaire (ERI)	-	✓	-	✓	-
Job Crafting Scale (JCS) - adapted	-	✓	-	✓	-
Treatment Inventory of Costs in Psychiatric Patients (TIC-P), subscale for productivity loss	-	✓	-	-	✓
Health and Labor Questionnaire (HLQ)	-	✓	-	-	✓
Assessment of Quality of Life (AQoL-6D)	-	✓	-	-	✓
Client Satisfaction Questionnaire (CSQ/CSQ-I)	-	-	-	✓	-
Preferences for online and group stress management - self-developed	-	✓	-	✓	-
Adherence to the intervention - self-developed	-	-	-	✓	-
Beck Depression Inventory (BDI), suicide ideation item	✓	-	-	-	-
Socio-economic variables (staff headcount, including income from paid employment, history of health service use, current health-related change programs in the organization, preference for Internet-based vs. in-person group training for stress reduction)	✓	-	-	-	-

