Note: T0 = Screening for eligibility; T1 = Baseline Assessment; T2 = Pre-Intervention Assessment prior to intervention beginning; T3 = Post-Intervention-Assessment, 3 months after group allocation; T4 = Post-Intervention-Assessment, 6 months after group allocation

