### Statistical analysis

### Sample size

We used a multi-method approach to calculate the sample size required for this trial [69]. Sample size was calculated using a non-inferiority criterion, based on previous meta-analytic evidence for the reference group (gSMT). In a systematic meta-analysis, Richardson & Rothstein identified an effect of d = 0.73 on stress reduction for occupational stress management interventions, relative to being on a waiting list [10]. This effect would correspond to 4.6 points on the PSS, assuming a standard deviation of 6.3 points, derived from normative sample data from German employees [50]. In addition, we took anchor-based clinical judgement of a meaningful difference in primary outcome measure scores into account. We conducted two focus groups with clinical (*n* = 4) and occupational health experts (n = 4). All the focus group members agreed that a reduction of at least 3 points on the PSS would display a meaningful difference for people with elevated levels of stress at baseline (PSS score ≥ 22). Finally, we set the non-inferiority margin ∆ at 2 points on the PSS at T3. Based on the predefined margin, we need 314 subjects to reject the null hypothesis of inferiority of the iSMT with 80% statistical power, assuming deterioration of not more than 2 points relative to gSMT, with two-sided α = .05. Based upon previous studies on the Internet-based intervention [29, 30], we expect that approximately 30% of participants will drop out of the study during the intervention phase (between T1 and T3). Accordingly, we aim to recruit 448 participants.

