### Study limitations

Despite the potential contributions of the present study, several limitations must be considered. First, participants allocated to the Internet-based condition will be offered immediate access to the online intervention, whereas participants assigned to the in-person intervention will have to wait some time before their first workshop session. Although we will make efforts to hold the workshops promptly and to schedule these training workshops as soon as possible, we expect that people in this intervention group will start considerably later than those assigned to the Internet-based treatment group. This said, this difference between these two interventions reflects the real-life characteristics of the two training formats and contribute to the study’s external validity. Second, group allocation cannot consider participant preferences, which limits conclusions regarding the implementation and actual reach of the two formats in the general employee population [74, 75]. Due to the randomized trial design, it is difficult to compare the attractiveness of the two interventions, in terms of uptake rates. Consequently, whether the Internet-based intervention shows non-inferiority or even superiority over group-based training, it remains unclear which training format would reach more employed individuals and make a greater contribution to stress reduction in the population. In psychotherapy, surveys suggest that people prefer traditional over digital care [76], but little is known about employees’ preferences regarding SMT. To address these issues, we will measure participants’ preferences towards the two intervention formats. Insights from this trial will provide a basis for allocating resources to iSMT or gSMT and facilitate future studies offering participants the opportunity to choose their preferred format. Third, digitalization of the intervention format (Internet-based vs. in-person) may be the most obvious distinctive feature of the two interventions in the present study. However, the interventions differ in several other characteristics, like the social context (individual-based vs. group-based training), major coping strategies used (problem solving plus emotional regulation techniques vs. problem solving plus cognitive restructuring), and mode of communication (asynchronous vs. synchronous). Therefore, findings from this trial cannot be attributed solely to one interventional feature. Nonetheless, the two interventions have in common that they have already been evaluated in randomized controlled trials, are offered widely in routine practice nationally, are considered gold-standard programs for either iSMT or gSMT, and offer real-life scenarios for the delivery of Internet-based and traditional healthcare programs for stress prevention [77]. Finally, participants will experience stress elicited by a great variety of work-related stressors. The Effort-Reward-Imbalance Questionnaire as a short measure for work-related stressors is unlikely to provide a multidimensional picture of the workplace situation according to, for example, the Health and Safety Executive Management Standards [78]. This would require more detailed and substantially longer assessments. However, identifying the sources of stress in detail is a complex task and require elaborated epidemiological research that is hardly feasible to conduct alongside an intervention study.

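### QALYs are to come from the AQoL-6D at baseline and month 6 only, so the cost-utility result ignores the path in between, where the two arms are expected to start at different times

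*Protocol article*

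**What the plan says.** The section Cost-effectiveness measures commits the trial to QALYs: "For cost-utility analyses, we will calculate quality-adjusted life years (QUALYs), based on the Assessment of Quality of Life (AQoL-6D". In Table 3 (under Primary outcome), the row for the "Assessment of Quality of Life (AQoL-6D") is ticked at T1 and T4, with dashes at T0, T2 and T3. The table note fixes the times: "T3 = Post-Intervention-Assessment, 3 months after group allocation" and "T4 = Post-Intervention-Assessment, 6 months after group allocation".

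On the start of training, Study design says that "participants in iSMT will be granted access to the intervention immediately after randomization", while gSMT participants wait until a group can be filled. Study limitations adds: "we expect that people in this intervention group will start considerably later than those assigned to the Internet-based treatment group".

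The article gives no QALY formula, no utility values and no waiting time. Economic evaluations describes cost-benefit and cost-effectiveness analyses and does not return to the cost-utility analysis.

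**The concern.** A QALY is utility accumulated over time. With utility known only at the two ends of a six-month window, everything between has to be assumed, and linear interpolation imposes the same straight-line shape on both arms. The protocol itself expects the arms to differ inside that window, because one starts at once and the other after a wait.

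Study limitations defends the wait as a real-life feature of the two formats, and the Discussion lists availability among the possible advantages of iSMT. An economic measure that gives no credit for earlier benefit leaves out part of what the comparison is meant to value.

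The schedule is also something that a later analysis plan cannot mend: utilities not collected at T3 cannot be recovered.

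**Working it through.** The plan states no QALY figure, so there is none to reproduce. The check works out what the schedule implies.

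**Inputs from the article.** AQoL-6D at T1 and T4 (Table 3). T3 at 3 months and T4 at 6 months after allocation (note to Table 3), that is 0.25 and 0.5 years, or weeks 13 and 26. iSMT has seven modules on a weekly schedule; all gSMT training days fall within seven weeks.

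**Assumptions.** Linear interpolation between measurements; T1 taken as time 0; equal mean utility at T1. The utility differences and waiting times below are illustrations, since the article gives none.

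**Step 1: weights.**

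- Two points (as scheduled): 0.5 × (U_T1 + U_T4)/2 = 0.25·U_T1 + 0.25·U_T4.
- Three points (T3 added): 0.125·U_T1 + 0.25·U_T3 + 0.125·U_T4.

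T3 would carry 0.25 of a total weight of 0.5, that is half.

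**Step 2: between-arm difference.** Let d3 and d4 be the utility differences (iSMT minus gSMT) at T3 and T4. The two-point difference is 0.25·d4. The three-point difference is 0.25·d3 + 0.125·d4.

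| d3 | d4 | Two-point | Three-point | Two-point relative to three-point |
|---|---|---|---|---|
| 0.03 | 0 | 0 | 0.0075 | missed entirely |
| 0.03 | 0.03 | 0.0075 | 0.01125 | understated by a third |
| 0 | 0.03 | 0.0075 | 0.00375 | overstated twofold |
| 0.03 | −0.01 | −0.0025 | 0.00625 | sign reversed |

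The signs differ only if d3 and d4 have opposite signs and 0.25·|d3| > 0.125·|d4|, that is |d3| > |d4|/2.

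**Step 3: a delayed start.** Suppose both arms reach the same gain U, linearly over seven weeks, with iSMT starting at week 0 and gSMT at week w. For w up to 19 (26 − 7), both arms have the full gain at T4, so d4 = 0 and the two-point difference is 0. The true difference is (w/52)·U. For w from 6 to 13, d3 = U × [1 − (13 − w)/7], and the three-point difference is 0.25·d3. For w up to 6, gSMT has the full gain by week 13, so d3 = 0.

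| Wait w (weeks) | True difference | d3 | Three-point | Two-point |
|---|---|---|---|---|
| 6 | 0.115·U | 0 | 0 | 0 |
| 8 | 0.154·U | 2/7·U | 0.071·U | 0 |
| 10 | 0.192·U | 4/7·U | 0.143·U | 0 |
| 12 | 0.231·U | 6/7·U | 0.214·U | 0 |

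For an assumed U of 0.02 to 0.10 and a wait of eight weeks, the true difference is 0.0031 to 0.0154 QALY, the three-point estimate 0.0014 to 0.0071, and the two-point estimate 0.

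**The case against.** The strongest objection is that T3 may add little. Table 3 labels T3 a post-intervention assessment, and gSMT can take up to seven weeks. If it takes all seven, T3 at week 13 is post-intervention only when the wait is at most 13 − 7 = 6 weeks. In the model above, that is the range in which the three-point estimate misses the onset effect completely. The authors also say that they will schedule workshops as soon as possible. This stands as a limit on the remedy. It does not remove the concern, because no maximum wait is given and the authors expect a considerable one.

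Other objections also hold in part:

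- The straight line is an inference, since no QALY method is named. But any QALY built from T1 and T4 alone lacks a utility at T3.
- The cost questionnaires (TIC-P and HLQ) share the T1 and T4 schedule, so adding the AQoL-6D alone refines effects and not costs.
- T3 is the primary-endpoint assessment and already carries nine measures. About 30% dropout is expected by then, so extra burden there is not free.

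A reader might go further and infer that the planned QALY can show nothing that happens before T4. That is too strong: a difference that lasts to T4 is partly counted. Nor does an early benefit that merely fades to equality turn the sign. It gives zero, and reversal needs the arms to cross.

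**Conclusion.** The point holds as a limitation of one secondary economic analysis. With the AQoL-6D at T1 and T4 only, and assuming linear interpolation and equal baselines, the QALY difference is 0.25 × the T4 utility difference whatever happens between. A persisting difference is attenuated, by a third when d3 = d4. One that has gone by T4 is lost. The sign errs only if the arms cross with |d3| > |d4|/2.

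If both formats end at the same gain, the omission works against the earlier-starting iSMT. How far it does so in this trial cannot be said, because the article gives neither utilities nor waiting times; the figures above are illustrations.

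A reader might infer that the trial's main conclusion or its whole economic evaluation is at risk. The article does not support that. The primary analysis uses the PSS at T3, and the cost-effectiveness analysis uses reliable improvement in perceived stress at T4; neither uses the AQoL-6D. The change is a cheap improvement, not a condition for the trial's validity.

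**What to change.** Amend Table 3 to add the AQoL-6D at T3. Compute QALYs as the trapezoid over T1, T3 and T4, adjusted for T1 utility, and keep the T1–T4 version as a sensitivity analysis.

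State in the plan that this captures the difference in onset only in part: in the seven-week linear-gain model, not at all for waits up to about six weeks, and 0.071 of 0.154·U at eight weeks. The T2 assessment comes just before the first session and so dates each participant's start; report the observed waits beside the result.

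The cost is a schedule amendment and one more questionnaire in an online assessment that already takes place. The article does not give the length of the AQoL-6D, so the added burden cannot be put in minutes. Placing it after the PSS limits any effect on the primary endpoint.

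If T3 cannot be changed, state the linear-interpolation assumption and add a sensitivity analysis with other paths between T1 and T4.

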#### Potential moderators

We will explore potential moderating variables of iSMT and gSMT that might affect the comparative efficacy of the two interventions: participant age, gender, technology readiness, training experience (online vs. in-person group, yes/no), training expectations, and preferences for Internet-based or group training. To assess technology readiness, we will use the Technology Readiness Index 2.0 (TRI) [63]. We will use the Patient Questionnaire on Therapy Expectation and Evaluation (PATHEV) [64], adapted to stress-management training, to assess outcome expectancies and suitability, with regard to the training received. To explore the potential impact of workplace conditions on stress, we will use the German Version of the Effort-Reward-Imbalance Questionnaire – Short Form [65], which has reliably shown associations between work-related stress and both physical [4] and mental health [66] impairment. In addition, we will use the German version of the Job Crafting Scale, by Tims and Bakker [67, 68], which measures self-initiated changes that employees make in their own job demands and job resources to optimize their personal goals. We will use the three items with the highest item-scale-correlation for each subdomain [68], resulting in twelve questions for the whole scale. In addition, we will use self-developed questions to explore preferences for either of the training formats under study (e.g., for iSMT: “It was important, to me, that I was able to do the training at my own pace”; for gSMT: “It was important, to me, that I was in contact with other participants in one place”).

### Statistical analysis

### Sample size

We used a multi-method approach to calculate the sample size required for this trial [69]. Sample size was calculated using a non-inferiority criterion, based on previous meta-analytic evidence for the reference group (gSMT). In a systematic meta-analysis, Richardson & Rothstein identified an effect of d = 0.73 on stress reduction for occupational stress management interventions, relative to being on a waiting list [10]. This effect would correspond to 4.6 points on the PSS, assuming a standard deviation of 6.3 points, derived from normative sample data from German employees [50]. In addition, we took anchor-based clinical judgement of a meaningful difference in primary outcome measure scores into account. We conducted two focus groups with clinical (*n* = 4) and occupational health experts (n = 4). All the focus group members agreed that a reduction of at least 3 points on the PSS would display a meaningful difference for people with elevated levels of stress at baseline (PSS score ≥ 22). Finally, we set the non-inferiority margin ∆ at 2 points on the PSS at T3. Based on the predefined margin, we need 314 subjects to reject the null hypothesis of inferiority of the iSMT with 80% statistical power, assuming deterioration of not more than 2 points relative to gSMT, with two-sided α = .05. Based upon previous studies on the Internet-based intervention [29, 30], we expect that approximately 30% of participants will drop out of the study during the intervention phase (between T1 and T3). Accordingly, we aim to recruit 448 participants.

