**Methods:**

In a randomized, controlled, non-inferiority trial employees from the general working population will be allocated to iSMT or gSMT. The primary outcome will be perceived stress, assessed using the Perceived Stress Scale, three months after randomization. The non-inferiority margin for the primary outcome measure will be set at 2 points (Cohen’s d = 0.29). This trial will also compare the two interventions from a health economics perspective, and conduct explorative analyses to identify potential effect moderators.

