### Primary outcome analysis

Referring to the CONSORT guidelines for non-inferiority trials [27], our analysis of non-inferiority will be limited to participants who adhere to the study protocol (per-protocol analysis). That means we will only include participants who have been randomly allocated, have complete data, and attended at least five out of seven iSMT or gSMT sessions. To declare non-inferiority, the upper bound of the 95% confidence interval (CI) for the difference in mean scores on the PSS between iSMT and gSMT must be below the margin ∆. For non-inferiority, we also will conduct a separate analysis based on an intention-to-treat (ITT) sample, including all randomly-allocated subjects, to test for iSMT superiority with a one-sided alpha error set at α = .05. This procedure has been found appropriate for non-inferiority evaluations [27, 70]. For analysis of the primary outcome, we will use linear models adjusted for the baseline outcome value and stratification variable. The primary outcome will be perceived stress at T3.

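### The recruitment target of 448 allows for study dropout but not for the five-of-seven-sessions rule, so the stated 80% power is unsupported for the per-protocol set that decides non-inferiority

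*Protocol article*

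**What the plan says.** *Protocol article, Sample size.* The margin is 2 points on the PSS at T3. The only standard deviation given there enters as "assuming a standard deviation of 6.3 points, derived from normative sample data from German employees". The requirement reads "we need 314 subjects to reject the null hypothesis of inferiority of the iSMT with 80% statistical power". The significance level is given as two-sided 0.05. The one allowance for losses is that "we expect that approximately 30% of participants will drop out of the study during the intervention phase (between T1 and T3"), with two earlier studies of the internet programme cited as its source. The paragraph then concludes: "Accordingly, we aim to recruit 448 participants".

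*Protocol article, Primary outcome analysis.* Non-inferiority is tested in the per-protocol set only. To belong to it a participant must be randomised and must "have complete data, and attended at least five out of seven iSMT or gSMT sessions". The success criterion is an upper 95% confidence limit, for the iSMT minus gSMT difference in mean PSS, of less than 2 points. The model adjusts for the baseline PSS score and the stratification variable. The intention-to-treat sample, which is everyone randomised, serves a separate test of superiority at one-sided 0.05.

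**The concern.** Entry to the deciding set has two conditions after randomisation: complete data and enough sessions. The 30% allowance, as worded, concerns leaving the study, which corresponds to the first. Nothing is set aside for the second. A participant who answers the T3 questionnaire after four sessions is not a study dropout, yet is excluded from the non-inferiority test.

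The plan expects such people to exist. E-coaches send reminders when a module is overdue, trainers record attendance, and adherence is assessed at T3. In the group arm the seven sessions are packed into three days as 3 + 2 + 2 (Table 2), so missing day 1 alone leaves four of seven and excludes the participant.

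At stake is how a negative result is read. If the upper confidence limit crosses 2 points, readers will assume that a test with 80% power failed. It may instead reflect a smaller set than planned, and no figure was fixed in advance against which to judge that.

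**Working it through.** **Inputs.** Margin Δ = 2, SD = 6.3, two-sided 0.05 (one-sided 0.025 for non-inferiority), 80% power, 314 needed, 30% dropout and 448 recruited, all from *Sample size*. Two assumptions, neither stated in the article: a true difference of 0 and 1:1 allocation. Together they reproduce 314.

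**1. Reproduce 314.** For N analysed in equal arms, power comes from the noncentral t distribution with N − 2 degrees of freedom and noncentrality Δ / (SD × √(4/N)).
- N = 312: power 79.8%
- N = 314: power 80.1%

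So 314 is the smallest even total that reaches 80%.

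**2. Reproduce 448.** 314 / 0.70 = 448.6. In reverse, 448 × 0.70 = 313.6. The inflation is exactly used up by study dropout.

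**3. Apply the attendance rule.** Let a be the share of T3 completers with at least five of seven sessions. Only this group matters, because non-attenders who also leave the study are already in the 30%. Then N = 448 × 0.70 × a. With baseline adjustment, the SD becomes 6.3 × √(1 − r²), where r is the correlation between baseline and T3 PSS. The article gives neither a nor r, so both are assumed ranges.

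| a (assumed) | Per-protocol N | Power, unadjusted | r that fully offsets the loss, √(1 − a) | Recruits for 314 per-protocol, unadjusted: 314 / (0.70 × a) |
|---|---|---|---|---|
| 100% | 313.6 | 80% | 0 | 449 |
| 95% | 298 | 78% | 0.22 | 473 |
| 90% | 282 | 76% | 0.32 | 499 |
| 80% | 251 | 71% | 0.45 | 561 |
| 70% | 220 | 65% | 0.55 | 641 |

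For example, at a = 80%: N = 250.9, noncentrality 2 / (6.3 × √(4/250.9)) = 2.51, power 71%.

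**4. Credit for the planned adjustment, at a = 80%.**
- r = 0.3: SD = 6.3 × √0.91 = 6.01, power 75%
- r = 0.5: SD = 6.3 × √0.75 = 5.46, power 82%

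**5. Loss in one arm only.** With 156.8 T3 completers in one arm and 156.8 × (1 − q) kept in the other, unadjusted power is 78%, 75% and 72% for q = 10%, 20% and 30%. This is worth showing because the bundled group days and the weekly online modules may give different adherence.

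**The case against.** Four arguments deserve an answer.

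*The 30% may already cover both losses.* It is tied to the intervention phase and taken from earlier trials whose definition of dropout cannot be seen here. If it includes T3 completers with too few sessions, there is no shortfall. This stands as a possibility. But the wording speaks of leaving the study, and the cited trials concern only the internet programme, so nothing is offered for attendance in the group arm.

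*The planned analysis is more efficient than the calculation.* This largely stands. The calculation uses the unadjusted SD, while the model adjusts for baseline, so the unadjusted powers above describe a less precise test than the one planned. A reader might infer from them that the trial is underpowered. The article does not support that: with r of about 0.45, a 20% loss is fully offset. It does not support the opposite either, since it neither states a correlation nor claims the gain.

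*The size is assumed.* True: no adherence rate is given, and some features limit the loss. E-coaches send reminders, and missing only day 2 or only day 3 of the group training still leaves five of seven sessions.

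*A condensed article may leave this to the full protocol.* Detail, yes. But the article prints a finished calculation and an explicit primary set, and as worded the two do not match.

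It is also tempting to say that the 80% belongs to the intention-to-treat analysis instead. It does not. That analysis covers all 448 randomised and tests superiority. At the true difference of 0 that reproduces 314, it would reject at about its 5% error rate.

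**Conclusion.** The point holds in a limited form. Every stated figure reproduces, so this is not an arithmetic slip. The plan attaches 80% power to about 314 people with T3 data, while the non-inferiority decision rests on the subset of them with enough sessions. The two sets coincide only if all T3 completers are adherent. Unadjusted power falls to between 78% and 65% as assumed adherence goes from 95% to 70%. Baseline adjustment could restore part or all of this, depending on a correlation the article does not give.

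The conclusion is therefore that 80% is unsupported for the deciding analysis, not that true power is below 80% or that 448 is too few. It rests on reading the 30% literally as study dropout, on a true difference of 0 and on equal allocation.

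**What to change.** Rewrite the end of the *Sample size* paragraph so that it:

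1. says that 448 randomised, less 30% study dropout, gives about 314 participants with T3 data;
2. states the share of T3 completers expected to attend at least five of seven sessions, separately for each arm and with a source, and gives the resulting per-protocol size and non-inferiority power;
3. states the assumed baseline–T3 correlation and its source, if credit for the adjusted model is claimed.

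Alternatively, if the 30% was meant to cover both dropout and too few sessions, say so and justify it for the group arm as well as the internet arm.

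The 80% should not be reassigned to the intention-to-treat analysis, for the reason given above.

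The cost is a few sentences and a per-protocol power that may look less favourable. The margin, decision rule, analysis set and recruitment target are unchanged, and no extra participants are required.
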